### Interim analyses {21b}

In phase I, P2–P5 will receive a keratinocyte sheet with a 1-month interval after P1 for safety considerations. Moreover, all participants in phase I and II will be monitored at 3, 7, 10, 14, 21, and 28 days and 3 and 6 months after transplantation by consideration of any probable AEs and SAEs, and wound observation by the investigator. After the completion of the phase I clinical trial, all data includes AEs and SAEs, and wound healing process will be assessed and reviewed to confirm the safety of the process for starting the next phase. After the completion of the phase II clinical trial, all data from both phases will be analyzed.

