### Trial design {8}

Two consecutive clinical trials were designed, one of them is a phase I, non-randomized, open-label trial, and phase II is a randomized and open-label trial. The second phase will be started after the last follow-up of phase I study, if no SAEs related to the transplantation of keratinocyte sheet is reported. In these studies, we will evaluate the safety and efficacy of allogeneic cultured keratinocyte sheet transplantation for healing deep second-degree burn wounds as well as the superiority of this product to conventional treatments.

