#### Criteria for discontinuing or modifying allocated interventions {11b}

Once any reports of SAEs related to the product transplantation are documented, this trial will be terminated.

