### Outcomes {12}

The primary endpoint for this study is safety, which will be evaluated in all follow-ups by Common Terminology Criteria for Adverse Event (CTCAE), version 5.0 [27]. Furthermore, secondary endpoints of this project are time to wound epithelialization, skin graft take rate, scar assessment, wound closure, and quality of skin structure.

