#### Sample size {14}

To determine the necessary sample size for the study comparing the response rate between the control group and the intervention group, the formula for duplicate sizes in the two groups was used. It was assumed that four rounds of transplantation would be performed, with a mean correlation of 0.5 between repetitive interpersonal measures, a 5% first type of error, a statistical power of 95%, and a minimum difference in response rate of 45% based on similar studies [26–29]. Using these parameters, a sample size of 40 patients was estimated. In the first phase of the study, 5 patients will be included and in the second phase, and 35 patients will be enrolled based on the approved inclusion and exclusion criteria.$$n=\frac{{2\left( z_{\alpha/2}+ z_{\beta }\right)}^{2}{\sigma }^{2}\left\{1+\left(m-1\right)\rho \right\}}{{md}^{2}}$$

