## Statistical methods

### Statistical methods for primary and secondary outcomes {20a}

After enrollment of all patients, the data will be entered into the SPSS software for statistical analysis. Based on the distribution of data, paired sample *t*-test or non-parametric equal (chi-square test) will be used for comparing the difference in before and after sample data. For comparing each group in phase II, a Student *t*-test or chi-square test will be administered. Moreover, to handle missing data, a multiple imputation test will be used.

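### The tests named for the primary outcome cannot estimate safety, and no related SAE in 5 patients cannot confirm it

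*Protocol article*

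**What the plan says.** All references are to the protocol article.

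- **Endpoint.** Outcomes {12}: "The primary endpoint for this study is safety", graded with CTCAE version 5.0 at every visit. The other outcomes (epithelialization, graft take, scar, closure, skin structure) are secondary.
- **Named analysis.** Statistical methods for primary and secondary outcomes {20a} gives a paired t-test, or a chi-square described as its non-parametric counterpart, for before/after data. For phase II it adds: "For comparing each group in phase II, a Student *t*-test or chi-square test will be administered".
- **Layout of phase II.** Under Intervention description {11a} and Sequence generation {16a}, three wounds of the same patient are allocated to autograft, conventional treatment and keratinocyte sheet.
- **Size.** Sample size {14}: "In the first phase of the study, 5 patients will be included"; for phase II, "35 patients will be enrolled based on the approved inclusion and exclusion criteria".
- **Start of phase II.** Trial design {8} starts it "if no SAEs related to the transplantation of keratinocyte sheet is reported". Interim analyses {21b} says that after phase I the AEs, the SAEs and the "wound healing process will be assessed and reviewed to confirm the safety of the process for starting the next phase".
- **Stopping.** Criteria for discontinuing or modifying allocated interventions {11b}: "Once any reports of SAEs related to the product transplantation are documented, this trial will be terminated".

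**The concern.** The primary endpoint calls for an estimate: how often patients given the sheet have serious or severe events, and how high that risk could still be given the data. The methods section fixes tests of difference instead, and the trial's layout leaves those tests little or nothing to work on. Separately, the phase I review is described as confirming safety, with no tolerable rate and no confidence limit, although its explicit criterion is a zero count in 5 patients.

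At stake is what the trial may say about its primary endpoint. The Discussion puts the work forward in support of registering an off-the-shelf product, so the safety statement should be one the data can carry.

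**Working it through.** **1. The plan's own figure.** The only stated calculation is the total of 40 in Sample size {14}. Its inputs are two-sided alpha 5%, power 95%, m = 4, rho = 0.5 and d = 0.45. The variance is not stated; I assume the binary maximum, 0.25.

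n = 2(1.960 + 1.645)² × 0.25 × (1 + 3 × 0.5) / (4 × 0.45²) = 20.05 per group, or 40.1 in total.

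So 40 reproduces, but it is sized on a response rate. No figure in the document supports the safety endpoint.

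**2. The named tests set against the endpoint.**

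| Safety quantity | Named method | Why it does not fit |
|---|---|---|
| Events after transplantation | before/after test | there is no pre-transplant value to pair with |
| Patient-level events, phase II | t or chi-square between groups | each patient has all three treatments, so there are no separate groups of patients |
| Wound-local events, phase II | t or chi-square between groups | the three wounds share a patient, so they are paired and not independent samples |
| Related SAEs in a trial that completes | chi-square | all counts are zero, expected event counts are zero, and the statistic is 0/0 |

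For the third row, let b and c be the numbers of patients with an event only at the sheet wound and only at the comparator wound, with n patients. The within-patient risk difference is (b − c)/n, with estimated variance [(b + c) − (b − c)²/n]/n². An independent-sample chi-square uses only the marginal totals and ignores this pairing.

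**3. What zero related SAEs can show.** Assume independent patients with one related-SAE probability p each. The chance of no event in n patients is (1 − p)^n. The exact upper 95% limit for 0/n is 1 − 0.05^(1/n) one-sided and 1 − 0.025^(1/n) two-sided.

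| Data | One-sided | Two-sided |
|---|---|---|
| 0/5 | 45.1% | 52.2% |
| 0/35 | 8.2% | 10.0% |
| 0/40 | 7.2% | 8.8% |

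The document gives no SAE rate, so a range is shown:

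| True rate p | No event in 5 | No event in 40 |
|---|---|---|
| 5% | 77% | 12.9% |
| 10% | 59% | 1.5% |
| 20% | 33% | 0.01% |
| 30% | 17% | below 0.01% |

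The chance of no event in 5 equals one half at p = 1 − 0.5^(1/5) = 12.9%.

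**The case against.** The strongest reply is that the phase I sentence describes a gate, not the trial's conclusion. The review serves the start of phase II, and it covers AEs and wound healing as well as SAEs. Patients 2 to 5 are treated only after a one-month interval, and an independent DSMB sees the data and advises. Safety is then followed in 35 more patients, and {21b} has both phases analysed at the end. All of this stands, and it limits the wording problem to the claim made for phase I.

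Four stronger readings are tempting and are not supported:

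- *A harmful product would usually pass the gate.* The gate passes more often than not only below about 13%. At 20% it passes a third of the time. The documents name no harmful rate.
- *Phase II does not repair the weakness.* It largely does for related SAEs. Completing 40 patients without one has a 1.5% chance at a true rate of 10%, and it moves the one-sided limit from 45% to 7.2%. The zero count is implied by completion, but completion is itself informative.
- *The trial will announce safety as proven, or read a non-significant test as proof.* No section says so.
- *The chi-square would miss a known share of excess local harm.* Any such figure needs assumed event rates and treats the wounds as independent, so it gives no size for this point.

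It can also be said that interval methods belong in the SAP. That would answer a mere omission. Here the protocol does name methods for the primary outcome, and those methods do not fit it.

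**Conclusion.** The point holds in two parts. The main one is that {20a} fixes analyses for the primary outcome that cannot estimate it: they yield no absolute risk or bound, they assume separate groups where each patient carries all three treatments, and for related SAEs in a completed trial the chi-square does not exist. This follows from the document's own design and needs no assumed rate. Other AEs and unrelated SAEs are still recorded, so the endpoint as a whole is not fixed at zero.

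The second part is wording. No related SAE in 5 patients leaves rates up to 45% (one-sided) or 52% (two-sided) unexcluded, so it is preliminary evidence for a go decision and not confirmation. Those limits assume independent patients with a common risk; the pass probabilities also depend on the assumed rates shown.

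The data collection is sound. Only the analysis and the claim need to change.

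**What to change.** Leave the start and stopping rules as they are.

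1. **Interim analyses {21b}.** Describe the phase I safety result as preliminary, and report it with its exact upper 95% limit (if no related SAE occurs in 5 patients: 45% one-sided, 52% two-sided).
2. **Statistical methods {20a}, patient level.** Make the primary safety analysis the proportion of patients with a related SAE, and the proportion with any CTCAE grade 3 or higher event. Give Clopper-Pearson limits for phase I, phase II and both together. State in advance that 0/40 supports only a related-SAE risk below about 7% (one-sided) or 9% (two-sided).
3. **Statistical methods {20a}, wound level.** For wound-local events, replace the independent-sample chi-square with the within-patient risk difference, sheet minus each comparator. Give a 95% interval that respects the three wounds per patient; a score interval for paired proportions suits sparse counts. State that p > 0.05 will not be read as evidence of safety.

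The cost is a few sentences and one interval per safety outcome, with no extra patients, visits or procedures. The downside is that the stated safety conclusion becomes less favourable.

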### Methods for additional analyses (e.g., subgroup analyses) {20b}

N/a. In this study, we have not done any subgroup analysis due to the limited number of total patients.

### Methods in analysis to handle protocol non-adherence and any statistical methods to handle missing data {20c}

Multiple imputation includes the generation of multiple plausible values for compensation of missing data points, therewith preserving the uncertainty and variability associated with the missing data. Furthermore, sensitivity analyses will be conducted to evaluate the robustness of study outcomes to different assumptions about the missing data mechanism.

### Plans to give access to the full protocol, participant-level data and statistical code {31c}

All data generated during this study are included in this article. The results of this phase I and II trial will be published in scientific journals and will be available for researchers, clinicians, and patients.

### Oversight and monitoring

#### Composition of the coordinating center and trial steering committee {5d}

Principal investigator and research physician:Design of protocol and revisionsPreparation of CRF [case report forms]Publication of study reports

Trial management committee (TMC):Practical advice for the investigatorsRandomizationData validation

Data manager:Data entryData verification

Lead investigators:Patients’ recruitment, data collection, and completion of CRFs, doing the follow-up sessions

#### Composition of the data monitoring committee, its role and reporting structure {21a}

An independent Data and Safety Monitoring Board (DSMB) has been instituted, separate from the study coordinators. By the end of the phase 1 study, data analyses will be confidentially shared with the DSMB. Additionally, any supplementary analyses that the committee deems necessary will also be provided. These supplementary analyses might encompass data from similar trials for comparison. In this regard, the DSMB will advise the investigators.

#### Adverse event reporting and harms {22}

The primary endpoint for this study is safety, which will be evaluated in all follow-ups by Common Terminology Criteria for Adverse Event (CTCAE), version 5.0 [27]. All the data will be entered in CRF forms of the study.

#### Frequency and plans for auditing trial conduct {23}

The audit will assess the phase 1 clinical trial before the first visit of the first patient and after the final visit of the last patient. In phase 2, the audit will evaluate the study after enrollment of the 5th patients and 20th patients and at the end of the study.

#### Plans for communicating important protocol amendments to relevant parties (e.g., trial participants, ethical committees) {25}

Any alterations to the protocol that could influence the study’s implementation, potential patient advantage, or impact patient safety such as adjustments to study goals, design, participant demographics, sample sizes, study procedures, or substantial administrative elements will necessitate an official protocol amendment. Ethics Committee endorsement will be sought for such amendments.

#### Dissemination plans {31a}

All data generated during this study are included in this article. The results of this phase I and II trial will be published in scientific journals and will be available for researchers, clinicians, and patients.

## Discussion

In this study, we explained the design and rationale of a cellular-based skin substitute for the first time in Iran. It has been observed that almost £20,000 per quality-adjusted life year (QALY) is the annual cost of skin graft for 2nd-degree burn injuries [30]. Therefore, designing a substitute for skin grafting can help affected patients and reduces the invasive procedure of autologous skin graft. In addition, conducting this work proposes this product for being registered as an off-the-shelf product for burn wound management in the regulatory bodies of the country.

This project is novel to conduct in Iran; however, some limitations can exist in our work. First, many patients with 2nd-degree burn injuries may experience other trauma or co-existence morbidities, which can make the choice of eligible patients difficult for us. Second, due to its novelty, many patients may not collaborate to participate in this study. Third, many eligible patients may receive other treatment options, prior to transplantation, which can be a confounder for our intervention. We will address possible limitations in our first phase and will try to overcome our limitations in the second phase.

## Trial status

This is the protocol version 1 designed on 2022–04-25. Patients’ recruitment began on 7 November 2022. Patients’ recruitment will be completed on 30 November 2023, approximately.

## Data Availability

The results of both phase 1 and 2 studies will be published in scientific journals, and all necessary information will be available in the published manuscript and supplementary materials. Moreover, any extra information and datasheets will be available by sending a request to the principal investigator ([name]).

## Abbreviations

IRCT: Iranian Registry of Clinical Trials
CRF: Case report form
QALY: Quality-adjusted life year
VSS: Vancouver Scar Scale
POSAS: Patient and Observer Scar Assessment Scale
DSMB: Data and Safety Monitoring Board
